### Dissemination policy

The results of the present study will be disseminated by the Psychiatric Research Unit social media account and website. We will also seek to publish it through high-impact international peer-reviewed journals and present it at conferences for clinicians, commissioners, and researchers working in the mental health field. Both negative and positive findings will be published. The trial is registered at ClinicalTrials.gov (Nr 2,021,001). Although steps will be taken to avoid it, protocol deviations may happen. Protocol deviations that occur after the start of trial recruitment will be communicated at https://clinicaltrials.gov and detailed in publications.

### Trial status

The trial began recruitment in October 2021, and the last participant is expected to be included in January 2023. The experimental intervention ran from November 2021 to April 2023.

## Discussion

The current study will be the first RCT investigating MCA in a mental health service setting. It will be a feasibility study and will test the study hypothesis in a small clinical sample. If the present study is successful, it may be followed up by other, larger clinical studies on MCA. The study will contribute to sparse existing research concerning the impact of clinical assessment; it will provide important new knowledge about the effects of routine and systematic patient-centered clinical assessment and generate effect size measures for future power calculations. It will also generate data regarding patients’ readiness for psychotherapy, and the percentage of patients who are wrongly diagnosed in a prototypical Danish public psychotherapeutic healthcare clinic.

We believe that the intervention will have a positive effect on the included patients. However, there is a risk that the patients receiving MCA may not benefit from the excess assessment but that the treatment will instead increase dropout due to the patient becoming overwhelmed. There is also a possibility of the patients becoming upset or disappointed due to the new knowledge they receive about themselves. Ultimately, the MCA may yield an unexpected diagnosis which could severely change the way the patient sees herself and the way society in general sees the patient. Many of these problems may, however, also occur in AAU. We will evaluate this by comparison of dropout from MCA and AAU.

If the current project documents the feasibility of the approach, further studies should examine the incremental value of MCA on patient outcome in terms of treatment completion or number of treatment sessions attended, and cost-effectiveness.

By the end of the present project, we will be able to decide whether the results are sufficiently promising to pursue a full trial (phase III) [73]. For that purpose, the study output also encompasses the development of a MCA protocol for clinicians and an adjoining fidelity instrument.

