**Methods:**

We describe a randomized controlled feasibility and superiority trial of 42 individuals with a clinical diagnosis of either SP or AvPD, who are to initiate psychotherapeutic treatment in Danish outpatient mental health services. They will be randomized in a 1:1 ratio to either assessment-as-usual and receive no further assessment or to a Modified Collaborative Assessment (MCA) provided as a pre-treatment intervention before psychotherapy initiation. MCA will include a battery of psychological tests designed to thoroughly assess the patients’ psychopathology. The tests are administered in collaboration with the patient, including detailed oral and written feedback. We hypothesize that the intervention is feasible regarding patient’s acceptance and adherence. We further hypothesize that patients randomized to MCA will reach higher levels of readiness for psychotherapy as assessed with the University of Rhode Island Change Assessment Scale (URICA).

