### Objectives

The study objectives are to (1) explore the feasibility of MCA as an intervention through rates of recruitment of screened patients, patience’s adherence to MCA or Assessment As Usual (AAU), patient satisfaction ratings, and patient and therapist/clinician evaluations; (2) compare the effect of MCA versus AAU on levels of readiness for psychotherapy in patients referred to group therapy for social phobia or AvPD at end-of-intervention (T1) (main outcome) and after 1-month follow-up (T2); (3) compare the effect of MCA vs AAU on diagnoses (number of diagnostic revisions) and treatment offered (number of patients offered other or additional treatment) in patients referred to group therapy for social phobia or AvPD, as well as adherence to group therapy within the first 4 weeks; and (4) develop a fidelity checklist for the MCA intervention.

We hypothesize that MCA is feasible regarding acceptance and adherence in patients with social phobia or AvPD and is superior to AAU in increasing contemplation score (URICA, see below) at the end of intervention (T1). (2) In addition to this, patients offered MCA have higher service satisfaction ratings (CSQ) than those offered AAU prior to psychotherapy onset, and user evaluation scores of MCA (purpose-made) are positive (more than 3 on a 1–5 Likert Scale).

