### Experimental intervention

The MCA, as described in the “Introduction and rationale” section, will include the possible administration of the following nine assessment instruments:

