### Comparison intervention

Patients allocated to the control group will receive AAU, which is the standard assessment that patients receive in the clinic, administered as follows: the patients are referred to the clinic by a family doctor or a private practice psychiatrist. On intake to the clinic, they will receive a diagnostic interview with either a medical doctor or a psychologist which can be supplemented with specific psychological tests, (e.g., SCID-5) when personality disorders are suspected, depending on the current resources and competencies in the clinics and following request from the head of treatment. Supplementary assessment is indicated roughly in one case out of ten. Otherwise, AAU patients are on the waitlist for the group therapy and are not followed by any therapist. Following the end of the MCA intervention, MCA patients might also wait a short while for group therapy, not seeing any psychotherapist in that interval. As all participants start group therapy, they will have a designated contact person, but only one preparatory individual therapy session before entering the specific treatment group.

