### Data from Electronic Health Records (EHR)

We will monitor the number of no-shows and the number of diagnostic re-classifications by accessing the included patients’ EHR.

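### Diagnostic revisions can show the yield of MCA, but not diagnostic accuracy or a clinic-wide rate of wrong diagnoses, because only the MCA arm is systematically re-examined

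*Protocol article*

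**What the plan says.** - **Objectives, objective 3:** the trial is to "compare the effect of MCA vs AAU on diagnoses (number of diagnostic revisions", alongside treatment offered and early adherence to group therapy.
- **Data from Electronic Health Records:** the investigators will monitor "the number of no-shows and the number of diagnostic re-classifications" in the records of the included patients. Table 1 places this at T2, after four group sessions. Statistical considerations lists new diagnosis among the categorical outcomes.
- **Discussion:** the study is to produce "the percentage of patients who are wrongly diagnosed in a prototypical Danish public psychotherapeutic healthcare clinic". No arm, denominator or reference standard is named.
- **MCA arm:** Experimental intervention provides for "the possible administration of the following nine assessment instruments". The section on Modified Collaborative Assessment says the battery was chosen to pick up what a short interview can miss. The text after the list of instruments adds case supervision by a senior psychiatrist, whose purpose is to confirm or change the diagnosis.
- **AAU arm:** the Abstract describes "assessment-as-usual and receive no further assessment". Comparison intervention says "Supplementary assessment is indicated roughly in one case out of ten", and that otherwise "AAU patients are on the waitlist for the group therapy and are not followed by any therapist".
- **Entry:** under Participants and eligibility criteria the diagnosis at inclusion is tentative, and the sample is consenting patients with social phobia (SP) or avoidant personality disorder (AvPD), after exclusions.

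**The concern.** A diagnosis is revised only if somebody looks again. In MCA everyone is meant to be looked at again, with tools and supervision aimed at that purpose. In AAU few are. The difference in revisions therefore mixes two things: how often the intake diagnosis was wrong, and how often anyone checked. No common or blinded re-assessment of both arms is described that would separate them.

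Two misreadings are at stake. An excess of revisions in MCA could be taken as evidence that MCA makes diagnosis more accurate. The percentage promised in the Discussion could be quoted as an error rate for Danish public clinics, although about half of the sample was not systematically checked and the diagnosis being revised was provisional.

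**Working it through.** The protocol gives no figure for diagnostic revisions, so there is no figure of its own to reproduce. Its one sample size calculation concerns the URICA Contemplation score and does not bear on this point.

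**Inputs from the protocol.** N = 42 with 1:1 allocation, so 42/2 = 21 per arm. Supplementary assessment in AAU is about one case in ten, so r = 0.1.

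**Assumptions not in the protocol.** p is the true rate of wrong diagnosis, equal in both arms. s is the probability that re-examination detects it. All MCA patients are re-examined.

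**Step 1: expected revisions when the arms do not differ in true error.**

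MCA: p × s. AAU: r × p × s = 0.1 × p × s. The expected ratio is 1/0.1 = 10 whatever p and s are.

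**Step 2: effect of the denominator.**

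Pooled rate = (p × s + r × p × s)/2 = p × s × (1 + r)/2 = 0.55 × p × s. With s = 1 and p = 20%, 30% or 40%, the pooled percentage is 11%, 16.5% or 22%.

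**Step 3: chance that a two-sided Fisher exact test gives p < 0.05**, with 21 per arm and equal true error, summed over the two binomial distributions:

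| True rate in both arms | Expected MCA vs AAU (s = 1) | Chance, s = 1 | Chance, s = 0.8 |
|---|---|---|---|
| 10% | 10% vs 1% | 4% | 2% |
| 20% | 20% vs 2% | 30% | 18% |
| 30% | 30% vs 3% | 59% | 43% |
| 40% | 40% vs 4% | 79% | 64% |

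For single outcomes, 5 vs 0 gives p = 0.048 and 6 vs 0 gives 0.021, but 4 vs 0 gives 0.11 and 5 vs 1 gives 0.18.

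**Step 4: precision of the percentage.** The Clopper-Pearson limits for x of n are the 2.5% quantile of Beta(x, n − x + 1) and the 97.5% quantile of Beta(x + 1, n − x). For five revisions, all in MCA:

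- MCA arm: 5/21 = 23.8%, 95% CI 8.2% to 47.2%.
- All patients: 5/42 = 11.9%, 95% CI 4.0% to 25.6%.

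The count of five is illustrative.

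**The case against.** MCA is an assessment intervention, and finding what intake missed is one of its purposes. A higher number of revisions is then an intended effect. Objective 3 speaks of revisions and does not itself claim accuracy. This stands: the between-arm count is a legitimate measure of diagnostic yield.

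AAU patients can also be re-classified before the count. Some get supplementary tests. All who start group therapy have a contact person and a preparatory individual session, and the records are read at T2. MCA patients need not receive all nine instruments. This also stands: AAU is not systematically re-examined, rather than never re-examined, and the tenfold ratio above is an illustration, not a prediction.

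Three stronger readings are tempting, and the protocol does not support them.

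- **A significant difference is nearly certain.** It is not. It depends on an unknown true rate, and Step 3 runs from a few per cent to about 80%.
- **The plan divides by all 42 patients, so that unexamined AAU patients count as correctly diagnosed.** The record review covers all included patients, but nothing links it to the percentage in the Discussion, and no denominator is stated. Pooling is a possibility only. The choice of denominator could properly be left to the analysis plan.
- **Diagnostic revision is to be tested for superiority.** The superiority hypothesis concerns the Contemplation score. New diagnosis is listed as a categorical outcome with no test named for it.

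An analysis plan that is not shown could fix the denominator. It could not make ascertainment equal in the two arms.

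**Conclusion.** The concern holds in a limited form. By design, an excess of revisions in MCA is expected even with equal true error in both arms, so the comparison informs on yield and not on accuracy. The percentage promised in the Discussion cannot be delivered as worded, for three reasons: only the MCA arm is systematically re-examined, the entry diagnosis is tentative, and the patients are consenting SP or AvPD cases rather than the clinic's whole caseload.

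If all patients were used as the denominator, the percentage would be roughly half of that among re-assessed patients. The factor is 0.55 if one AAU patient in ten is re-examined and 0.50 if none is. It moves closer to 1 the more AAU diagnoses are reviewed before T2. The true rates and detection probabilities used here are assumptions.

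The point is minor. Record data are described among the exploratory outcomes and footnoted as a feasibility outcome in Table 1. The primary outcome, sample size and feasibility thresholds do not depend on them.

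**What to change.** 1. Estimate the percentage in the MCA arm, with patients who received the assessment as the denominator, and give an exact 95% CI. State how many MCA patients did not complete it, since non-completion may be related to diagnosis.
2. In the Discussion, replace the claim about wrong diagnoses in a prototypical clinic with *diagnosis revised after extended assessment in consenting SP/AvPD patients*.
3. Under objective 3, present the counts in both arms descriptively as the diagnostic yield of MCA, and say that they are not evidence on accuracy.

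This costs some wording and one table, and needs no new data. The drawback is precision. The rate rests on about 21 patients, or about 16 if completion only just meets the protocol's 75% adherence criterion (0.75 × 21 = 15.75), so the interval will be wide. That width should be shown, because it is all that the trial can say about this quantity.

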Like C/TA, MCA will include the administration of standardized diagnostic instruments, but in contrast to C/TA, we will only include a smaller selection of tests in order to secure feasibility. The battery of tests will be specifically designed to gather information on psychopathology which a brief clinical interview might not detect, such as symptoms of previously undetected developmental disorders or incipient psychosis. We have compiled a battery of tests with this focus because we find it most suitable for application in the Mental Health Service. The present study is further designed to establish diagnosis adhering to the current diagnostic systems (ICD-10 and DSM-5), but we expect it would also be applicable if the Mental Health Service introduced the dimensional [37, 38] model of psychopathology, since the current MCA also includes a thorough personality assessment according to the DSM-5 alternative model of personality pathology.

MCA emphasizes respect for the patients as “experts on themselves.” The assessor will, in collaboration with the patient, formulate a list of therapeutic questions which the patient would like to “ask the psychological tests.” This will help guide the patient and assessor’s collaborative quest to learn more about the patient’s problems and personal resources. The results of the assessment and the answers to the therapeutic questions will be communicated, respectfully, to the patient both orally and in writing. It will further be communicated to the patient’s future therapist in writing. In this manner, it should be possible to formulate personally relevant problems for later psychotherapy. The MCA assessor recognizes that diagnostic assessment is an interpersonal event and that the relationship between assessor and patient is paramount both in relation to the validity of the result and the patient’s further treatment [25].

In short, MCA is a brief, individualized, and person-centered assessment of psychopathology, where assessment, psychotherapy, and psychoeducation are integrated into a novel intervention, all carried out in collaboration with the patient.

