## Methods

### Design

The present protocol is based on reporting guidelines from the SPIRIT guideline for Standard Protocol Items for Clinical Trials [45] adapted as recommended when reporting protocols of feasibility trials [46]. The study is designed in order to inform and evaluate the feasibility of a possible future, full-scale RCT of MCA versus AAU. We will evaluate the feasibility of the interventions in terms of clinician resources and patient’s acceptability and adherence to the intervention and comparator, selected based on recommendations for the conduct of feasibility trials [47–49].

In addition to these feasibility outcomes, we will assess outcomes regarding readiness for change, symptoms, and regarding self-esteem and self-efficacy. Data are gathered from patients through a number of questionnaires delivered by the RedCap © webmodule prior to randomization (T0), at the end of MCA (T1) and after 4 weeks of psychotherapy (T2)—the absolute time depends on clinical logistics and timing of group therapy onset.

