#### Outcomes’ objective 1: Feasibility

Acceptability: The feasibility criterion for acceptability in patients is supported if 25% of patients who are found eligible for inclusion and who have received formal information (information meeting with the first author) about the trial agree to participate in the trial.Satisfaction: The feasibility criterion for satisfaction in patients is supported if the mean CSQ-8 score is ≥ 3 (see below for description of instrument).Adherence: The feasibility criteria for adherence in patients is supported if 75% complete the MCA intervention (attend all MCA sessions including feedback-session).Time spent on the intervention: We evaluate the resources used to complete the study by recording the time spent in direct contact with the patient used to complete the MCA intervention [48].Evaluation of the Intervention Questionnaire (EQ)Adverse events

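### Dropout is the only stated measure for three named harms but suits only the first; the later data that could show the other two are not linked to them

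*Protocol article*

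**What the plan says.** The Discussion of the protocol article lists three ways in which MCA might do harm:

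1. The extra assessment may not help, and "the treatment will instead increase dropout due to the patient becoming overwhelmed".
2. "There is also a possibility of the patients becoming upset or disappointed due to the new knowledge they receive about themselves".
3. "the MCA may yield an unexpected diagnosis which could severely change the way the patient sees herself", and also how society sees the patient.

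After remarking that many of these problems may also occur under assessment as usual (AAU), it states one evaluation for all of them: "We will evaluate this by comparison of dropout from MCA and AAU". Dropout is not defined there.

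The feasibility section (Outcomes' objective 1) treats the adherence criterion as supported if "75% complete the MCA intervention (attend all MCA sessions including feedback-session"). The section on modified collaborative assessment says that the results "will be communicated, respectfully, to the patient both orally and in writing".

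The Design section adds that, beyond feasibility, "we will assess outcomes regarding readiness for change, symptoms, and regarding self-esteem and self-efficacy". Table 1 schedules LSAS (social anxiety), RSES (self-esteem), GSES (self-efficacy) and PROM (including well-being) at T0, T1 and T2. LSAS, RSES and GSES are secondary outcomes and PROM is exploratory. None is described as a harm measure.

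**The concern.** The second and third harms are states of mind. They follow from what the patient learns, and a patient can experience either one without leaving anything. Retention is therefore an indirect measure of them. It is weaker still if dropout from MCA is counted by session attendance, because the session at which results are given is part of what makes a patient a completer.

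This matters for three reasons. The abstract lists safety among the things the trial assesses. The Discussion says that the results will inform the decision on a phase III trial. And the third harm is foreseeable: the battery is chosen to detect conditions that a brief interview may miss, such as undetected developmental disorders or incipient psychosis, whereas AAU adds supplementary assessment in roughly one case in ten. Similar dropout in the two arms could be reported as the answer to all three risks when it answers only the first.

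**Working it through.** The plan gives no figure for this point, so the check sets the sections side by side and then adds small illustrations. The 21 per arm is the planned 42 patients split 1:1.

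**Step 1. Match each harm to the stated measure.**

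| Harm (Discussion) | When it can arise | Does dropout register it? |
|---|---|---|
| Overwhelmed | During the assessment sessions | Yes; the harm is worded as dropout |
| Upset or disappointed by new knowledge | Mainly when results are communicated, possibly earlier | Only if the patient leaves, and leaves at a point the definition covers |
| Unexpected diagnosis, changed self-view | When the diagnosis is communicated, and afterwards | As above |

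**Step 2. Try both readings of dropout.** Assume that 4 of 21 MCA patients are distressed by the feedback (4/21 = 19%) and that nobody else leaves.

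| Assumed course | Dropout from MCA sessions | Dropout from the arm, including later therapy |
|---|---|---|
| All 4 withdraw after feedback | 0/21 (adherence 21/21 = 100%) | 4/21 = 19% |
| All 4 stay | 0/21 | 0/21 |

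The wider reading recovers those who leave. Neither reading recovers those who stay.

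**Step 3. Look for other data recorded at or after feedback.**
- Adverse events, checked at every clinic visit, with suicidality as the emphasis but not the limit (Adverse effects).
- The evaluation questionnaire (EQ) at the end of the intervention, and CSQ-8 satisfaction at T1 and T2.
- No-shows and diagnostic re-classifications from health records.
- Adherence to group therapy in its first 4 weeks, compared between arms (Objectives).
- RSES, GSES, LSAS and PROM at T0, T1 and T2.

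So relevant information exists. What is missing is a statement that any of it will be used to judge the second and third harms. EQ and CSQ-8 record evaluation and satisfaction rather than deterioration, and a count of re-classifications says nothing about how the patient took the news.

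**Step 4. How informative is dropout even for the first harm?** Assume 15% dropout under AAU, borrowed from the attrition allowance in the sample size section, and a two-sided 5% test of two proportions with n = 21 per arm:

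power = Φ{ [ |p1 − p2|·√n − 1.96·√(2·p̄·(1 − p̄)) ] / √( p1(1 − p1) + p2(1 − p2) ) }

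For 15% vs 30%, p̄ = 0.225. The numerator is 0.15 × 4.583 − 1.96 × √0.34875 = 0.687 − 1.157 = −0.470. The denominator is √0.3375 = 0.581. Power = Φ(−0.809) = 21%. The same formula gives about 44% for 15% vs 40% and about 80% for 15% vs 55%. An unremarkable dropout comparison would be weak reassurance even where the measure fits.

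**Step 5. What precision would a count of worsened patients have?** Assume 4/21 worsen under MCA and 1/21 under AAU. The difference is 3/21 = 14.3 percentage points. Its standard error is √(0.1905 × 0.8095/21 + 0.0476 × 0.9524/21) = √(0.00734 + 0.00216) = 0.0975. The simple 95% interval is 14.3 ± 1.96 × 9.75, about −5 to 33 points. That is wide and descriptive only.

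**The case against.** The strongest reply is that the trial does not depend on dropout to see harm. Adverse events and the EQ are listed feasibility outcomes. Self-esteem, social anxiety and well-being are measured in both arms at all three time points, and a between-arm comparison would show worse scores under MCA as readily as better ones. Patients who left after feedback would appear as failures to start or attend group therapy and as missing T2 data. Harm margins are also detail that a statistical analysis plan may supply; the article promises one and it is not shown here.

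Much of this stands. A reader might infer that the harms cannot be registered at all because the measure closes at the feedback session. The document does not support that, for four reasons:

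- The adherence criterion is a feasibility threshold, not a definition of dropout. Since AAU patients have no sessions after intake, dropout from the two arms is a natural reading and can extend past feedback.
- New knowledge can emerge in earlier collaborative sessions, where even session dropout could capture it.
- The adverse event check need not lapse after feedback. The text says only that "MCA patients might also wait a short while for group therapy, not seeing any psychotherapist in that interval", and those who start group therapy then have a contact person and a preparatory session.
- The data in step 3 are recorded at or after feedback.

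Two things survive. The Discussion makes a positive statement of how these harms will be evaluated, so this is not silence left to another document. And a mean comparison planned to show benefit can average out a few patients who got worse.

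**Conclusion.** The point holds as a mismatch between measure and harm. Comparing dropout suits one of the three named harms and is a poor measure of the other two, because a distressed patient who stays is not counted on any definition and a patient distressed at feedback already counts as having completed MCA. It does not hold that the harms are invisible to the trial: the data are there but are not linked to them. The practical risk is one of interpretation, with no excess dropout being read as no harm.

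The size cannot be derived from the document. The 4 of 21 is an assumption that shows the mechanism and is not an estimate. The conclusion rests on reading the Discussion sentence as covering all three harms, which its position after the whole list supports. It is a worthwhile, inexpensive correction and does not affect the primary outcome.

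**What to change.** In the Discussion statement, and in the statistical analysis plan that carries it:

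- Keep the comparison of dropout for the risk of being overwhelmed, say what counts as dropout in each arm, and state that dropout alone does not evaluate the other two risks.
- For those two, pre-specify a descriptive harm table: the number of patients per arm who worsen beyond a fixed margin (for example reliable change) on RSES, PROM well-being and LSAS, from T0 to T1 and from T0 to T2, with the between-arm difference and 95% CI. Give the number assessed per arm as well, since patients who leave may not return the T2 forms.
- Report MCA completers who do not start group therapy separately from MCA dropouts.

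No separate rule on the timing of T1 is needed, since the Design section already places it at the end of MCA.

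The cost is a few lines of text and one table from data already scheduled in both arms. The article reports that the intervention ran to April 2023, but nothing here needs new data collection, and the analysis plan is due before data processing starts. The drawbacks are that a margin must be chosen and justified, and that three scales over two intervals at about 21 per arm will give wide intervals. The table should be presented as description, not as a test of safety.
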